**\*\* Madaus, S.A. \*\***

## 1. SUMMARY

|                                                       |                                                                                                                                                                                                                                                                                                                                                         |
|-------------------------------------------------------|---------------------------------------------------------------------------------------------------------------------------------------------------------------------------------------------------------------------------------------------------------------------------------------------------------------------------------------------------------|
| Type of application                            | Clinical trial with an active substance of a medicinal product in new conditions of use.                                                                                                                                                                                                                                                                |
| Name of the sponsor                            | Madaus, S. A.                                                                                                                                                                                                                                                                                                                                           |
| Title of the clinical trial                    | Multicentre, comparative, double-blind, two-arm parallel clinical trial of the effects of treatment with Plantago ovata husk on the lipid profile of patients with hypercholesterolemia                                                                                                                                                          |
| Sponsor code                                   | PLAN-EC-HIPERL-02                                                                                                                                                                                                                                                                                                                                       |

| Trial phase                                    | Phase IV-II                                                                                                                                                                                                                                                                                                                                             |
| Objective of the trial                         | To determine the cholesterol-lowering effect of treatment with Plantago ovata husk in patients with moderate hypercholesterolemia in a low saturated fat diet                                                                                                                                                                                    |

|                                  |                                                                                                                |
|----------------------------------|----------------------------------------------------------------------------------------------------------------|
| Disease studied           | Patients with hypercholesterolemia, established as of LDL-C levels of $\geq 130$ mg/dl                         |
| Primary endpoint          | Reduction of LDL-C levels                                                                                      |
| Number of patients        | 290 patients                                                                                                   |
| Duration of the treatment | The treatment will last 8 weeks, although it may be prolonged for a further 8 weeks depending on the response. |
| Duration of the study     | Start: July 2005
Recruitment phase: 6 months
End: September 2006                                         |

### 3. INFORMATION

#### **A. Identification of the Trial**

**Code:** PLAN-EC-HIPERL-02  
Version No. 3 of 1.09.2004

**Title:** Multicentre, comparative, double-blind, two-arm parallel clinical trial of the effects of treatment with *Plantago ovata* husk on the lipid profile of patients with hypercholesterolemia

#### **B. Type of Clinical Trial**

Clinical trial with a medicinal product, phase IV-II (exploratory-therapeutic)

#### **C. Description of the investigational products**

##### **Investigational drug:**

Generic name: *Plantago ovata* husk  
Presentation: Sachets with 5 grams of granulate. Corresponds to 3.5 g of fibre.  
Sample manufacturer: Madaus S. A.  
Trade name: Plantaben

##### **Placebo:**

Microcrystalline cellulose + excipient

## 4. RATIONALE AND OBJECTIVES

### 4.1. *Rationale*

Cardiovascular diseases affect more than 30% of the population of the world's developed countries, and more specifically in Spain they account for more than 36% of deaths.

One novel aspect of the therapeutic programme is the importance being acquired by non-pharmacological instruments, including diet and physical activity, with a view to reducing the risk of presenting coronary and cardiovascular diseases. This new approach, called therapeutic life-style changes, has two purposes, on the one hand the prevention and treatment of the high levels of low density lipoprotein cholesterol (LDL-C) in plasma, the greatest risk factor in cardiovascular diseases. On the other hand, these measures target the reduction of the presentation of the actual cardiovascular events.

For all these reasons, diet-based therapy is the cornerstone of strategies for lowering plasma LDL-C and for reducing the risk of cardiovascular disease. Nevertheless, the optimal diet for protecting against cardiovascular diseases is a question of research and debate.

For many years, care has focused on the intake of fat and the replacement of saturated fatty acids by mono- and polyunsaturated fatty acids. Subsequently, the intake of carbohydrates has been well studied, and part of the interest lies in the relationship between different fibre-rich foods and in whether the type of fibre (soluble or insoluble) or the different types of fibre provided by foods (wholemeal cereals, fruits, greens and vegetables) can have a protective cardiovascular effect.

Ascertaining the quantity of fibre present in the food presents methodological difficulties, and in most cases the data used come from food composition tables. In our medium, the fibre content of the majority of foods of vegetable origin was determined directly, and the intake is estimated at about 828 g daily (about 576 g of greens, vegetables and fruit; 233 g of cereals, 312 g of legumes and 8 g of dried fruits). The quantity of total fibre is 18.5 g and soluble fibre 6.5 g a day. These quantities are typical of a Mediterranean country and express better consumption conditions, since in practice and in our environment only 20% of the population eats these quantities.

***What are the key elements of the diet in reducing levels of LDL-C and cardiovascular diseases?***

At the moment, strategies focus on reducing the content in fatty acids to less than 7% of total energy and less than 200 mg daily of cholesterol. Furthermore, the intake of *trans*-type fatty acids should be low, less than 2% of total energy.

These cholesterol-lowering measures can be optimised through the introduction of viscous (soluble) fibre and vegetable sterols or their saturated (stanol esters) form.

***What are the current recommendations on fibre intake to reduce cholesterol?***

In the United States, values have been dictated for total food fibre (Dietary Reference Intake, DRI) for the first time ever and generally, and are between 38 and 25 g a day, on the basis of 14 g of fibre per 1000 Kcal. The Adult Treatment Panel (ATPIII) proposes an intake of 10 to 15 g of viscous (soluble) fibre to reduce plasma LDL-C.

The addition of soluble fibre provided by food and by the psyllium, pectin, oats or guar supplements can have an additional cholesterol-lowering effect over and above that which is attained with the reduction of saturated fatty acids (<7% of total energy) and the reduction of the intake of cholesterol (<200 mg/day).

In Europe and Spain, the cardioprotective diet is addressed in the context of a healthy life-style, although the recommended quantity of fibre is not specified.

***Do foods cover total and soluble-type fibre needs?***

If the data on vegetable origin food of our environment are taken into account, and in the optimal, albeit minority situation, in the best of cases the daily intake of total fibre is 18 g and that of soluble fibre is 6 g.

If the recommended quantities of viscous (soluble) fibre are between 10 and 25 g daily, only 6 g a day are provided with a high intake of vegetable-origin food from the diet. Thus, soluble fibre supplements play an important role in reaching the recommended quantities. One factor that should be taken into account is the viscosity of soluble fibre, as it seems to be the determining factor in the mechanisms of action on the metabolism of cholesterol.

## **Efficacy**

### ***What is the effect of soluble fibre on LDL-C?***

The effect of the intake of 10 g of soluble type dietary fibre in the context of a low saturated fat diet produces a reduction of 5% in plasma LDL-C.

Generally speaking, the intake of 10 g of soluble fibre daily is thought to reduce LDL-C by 5%. This effect can also be assessed as 10 g of soluble fibre producing a reduction of 7.5 mg/dl of LDL-C.

### ***What does the individual response to soluble fibre depend on?***

Each one of the metabolic steps involved (absorption, transport, storage) is regulated by a large number of genes that interact with each other and with the environment. These genes present relatively common variations in the general population, called polymorphisms. There is one for every 200 nucleotides, about 10 million in the genome, of which 250 in 15 genes are related to the lipid metabolism.

Despite high genetic variability, there is a number of genes which by virtue of their functional importance or the prevalence of relevant mutations in the population, may be regarded as very determinant genes.

More specifically, the individual response to food changes may be explained by some of the polymorphisms involved in the metabolism of LDL or HDL. More specifically, the response of LDL-C may be related to the polymorphisms of apolipoprotein E, the levels of high-density lipoprotein cholesterol (HDL-C) to the polymorphisms of the cholesterol ester transfer protein (CETP), and triglyceride plasma concentrations to the polymorphisms of apolipoprotein A-V. The intake of soluble fibre is subject to individual factors and it is unknown whether there is a specific polymorphism that intervenes in fibre mechanisms on lipid metabolism, although on the basis of our previous results, the polymorphisms of the Fatty Acid Binding Protein (FABP type 2) at intestinal level in charge of the absorption of fatty acids could be candidates.

The fact that viscous (soluble) fibre increases the losses of bile acids at intestinal level renders it necessary to look for specific genes at this level of metabolism.

## **Safety**

### ***What are the adverse effects of the intake of soluble fibre?***

Alterations of bowel movement such as flatulence and abdominal distension may present with the intake of soluble fibre at the beginning of treatment, but will disappear after a few days of follow-up.

The interaction between soluble fibre and the absorption of liposoluble vitamins and minerals must be recorded, although in most studies no changes have been detected between the group of patients taking soluble fibre and placebo consumers.

### ***What is the aim of this study?***

The effect on plasma lipids of the soluble fibre obtained from the husk of *Plantago ovata* seeds is somewhat unknown, although some studies using this type of fibre are beginning to be published. This fibre is marketed in Spain as a medicinal product and its extension to the rest of Europe is being addressed.

If soluble (viscous) fibre can optimise the effects of the cholesterol-lowering diet (reduction of the content of saturated fatty acids and cholesterol), supplementing this type of fibre takes on special relevance.

Our interest lies in ascertaining the cholesterol-lowering effect of a specific type of soluble fibre present in the husk of *Plantago ovata* seeds.

The intake of a high quantity of fibre-rich vegetable origin products provides about 6 g of soluble fibre a day. In most cases, besides boosting the intake of this type of food, treatment with a *Plantago ovata* husk product contributes to achieving the recommended 10 to 25 g of soluble fibre in the diet, thus controlling the lipid profile.

Reality tells us that one part of the asymptomatic population presents a high cardiovascular risk due to the accumulation of several risk factors: gender, age, smoking, systolic blood pressure and cholesterol or total cholesterol/HDL cholesterol. A large part of the Spanish population are smokers (63%), another important percentage of the citizens have high blood pressure (higher than 40% [blood pressure  $\geq 140$  mm Hg or  $>90$  mm Hg or in treatment]) and half our population presents high blood cholesterol values (more than 200 mg/dl).

High blood pressure can also be modified by fibre, and its effect on blood pressure seems moderate and independent. However, there are no data on the action of *Plantago ovata* husk on the reduction of blood pressure levels.

In clinical practice, in order to reduce cardiovascular risk, aside from the diet, many patients require treatment with cholesterol-lowering drugs, mainly statins. For this reason, it will be interesting to provide data on the effects of the statins in combination with the administration of soluble fibre. This approach is based on the different modes of action of both: whereas viscous fibre increases the loss of bile salts through the intestine, the statins, by means of the inhibition of 3-hydroxy-3-methylglutaryl coenzyme A reductase, reduce the synthesis of cholesterol. Nevertheless, it has yet to be demonstrated whether the combination of a soluble fibre- and statin-based drug provokes a synergistic additive effect, or whether, on the other hand, its cholesterol-lowering effects are neutralised. This study uses simvastatin, a regular and low-cost statin, which has a proven cholesterol-lowering additive effect with a fibre-rich diet. Simvastatin at a dose of 20 mg a day provides a 20-30% reduction in LDL-C.

Treatment with statins will be initiated in patients who fail to reach desirable concentrations of 130 mg/dl of LDL-C with soluble fibre, and it will thus be possible to study the effects of the combination of soluble fibre and statins.

## Hypothesis

Soluble fibre may contribute to a reduction of LDL-C, and the combined effect with a statin (20 mg of simvastatin) may achieve an optimisation of the cholesterol-lowering effects in adults with several cardiovascular risk factors.

### 4.2. Objectives

#### **Primary endpoint**

To determine the capacity to *reduce by 5% the concentrations of plasma LDL-C* by treatment with soluble fibre –*Plantago ovata* husk– added to a low saturated fat diet in patients with moderate hypercholesterolemia.

#### **Secondary endpoint**

- To study the combined cholesterol-lowering effect of treatment with *Plantago ovata* husk and statins to achieve the therapeutic objective.
- To analyse the effect of *Plantago ovata* husk fibre on blood pressure.
- To study the effect of the combination of statins with *Plantago ovata* husk on blood pressure.
- To evaluate whether the response on plasma lipids is modulated by the polymorphisms of apolipoprotein E, cholesterol ester transfer protein (CETP), apolipoprotein A-V and FABP 2.
- Furthermore, possible variations of the effects of the soluble fibre and the statins according to the characteristics at the beginning of the study, LDL-C level, gender or BMI will be studied.

## **5. TRIAL TYPE AND DESIGN**

### **5.1. Development Phase**

Phase IV-II study

### **5.2. Detailed description of the randomisation process**

The eligible subjects will be randomly assigned to treatment A or B in a ratio of 1:1. With the aim of minimising potential bias in the result of this study because of the subjects, investigators or study personnel, in relation to the safety, efficacy or well-being of the study products, the study design will be double-blind. The subjects will be randomly assigned to treatment in a ratio of 1:1; the probability of any subject receiving either of the two treatments described for this study will therefore be 0.5.

The investigator or the study personnel will include subjects suitable to participate in the study sequentially by number of subject and centre, starting with the first patient and centre number of the numerical series assigned by MADAUS. The sponsor responsible for the randomisation will guarantee the randomisation code. The authorised personnel will provide the randomisation code.

The randomisation list consists of 09 centres, each centre containing 25 blocks of 4 patients per block; the final list being of 999 patients. This list has been programmed by Quintiles Trans. Version 8.2 of the SAS statistical package has been used.

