### **Visit S8 (Day 56± 3)**

The participants will go to the hospital for a visit addressing the following aspects:

➤ *Clinical*

A clinical history similar to that of S0 will be made

Identify the presence of clinical problems, concomitant treatments, etc.

Collection of adverse events.

Blood pressure and weight will be taken.

➤ *Analytical*

The results of the mean LDL-C value obtained in the two analyses made in the previous week (S7), at most 3 days before visit S8, will be noted. Similarly, the values obtained in the analyses on the last day of S7 will be noted as final parameters of the biochemistry and haematological trial.

➤ *Dietary*

The patients will already have returned the 3-day record the day they went to the hospital for the second blood sample extraction.

The dietician will address the diet follow-up and possible deviations. If the patient has to continue in the study he/she will be given diet guidelines according to his energy needs.

➤ *Medication*

Evaluate compliance with treatment with fibre. The patient should return used and unused medication containers.

**Two situations may arise at this point: 1) The patient has reached the therapeutic objective (LDL-C < 130) and will end the study, or 2) the patient will present an LDL-C ≥ 130 mg/dl and will continue with the same treatment with a statin (Simvastatin) added for a further 8 weeks.**

**The instructions on how to administer the fibre, the Simvastatin and, as the case may be, the patient's regular medication will be gone over once again.**

If the patient is to continue in the trial, the investigator will issue the same medication that the patient was taking + a statin in sufficient quantity for 4 weeks until visit S12.

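### The protocol tells the blinded investigators that every centre is randomised in fixed blocks of 4, and the printed list size (999) does not match its own construction (900)

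*Protocol*

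**What the plan says.** Protocol Section 5.2 sets out the allocation as follows.

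- Ratio: "The eligible subjects will be randomly assigned to treatment A or B in a ratio of 1:1".
- Masking: "the study design will be double-blind", with the stated aim of limiting bias from subjects, investigators and study staff.
- Order of entry: "sequentially by number of subject and centre, starting with the first patient and centre number of the numerical series assigned by MADAUS".
- Structure and total, for nine centres: "each centre containing 25 blocks of 4 patients per block; the final list being of 999 patients". No other block length is mentioned. The list is described as already programmed.

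Other sections bear on how an arm might become known. Section 9.4 has the individual code opened when a suspected serious and unexpected event is notified, and keeps the investigator blind only where that can be done. Visit S8 in Section 8.2 gives the investigator the mean of two LDL-C results, and Section 8.3.1 has each centre measure the lipid profile locally for that decision. The safety part of Section 4.1 says: "Alterations of bowel movement such as flatulence and abdominal distension may present with the intake of soluble fibre at the beginning of treatment". Section 6.5 expects 25 to 60 patients per centre over about 6 months, and Section 6.3 plans 290 patients in total.

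**The concern.** Blocking within centre is sound. The weakness is that its single length is printed in the document that site staff work from. With sequential entry, subjects 1 to 4, 5 to 8 and so on at each centre form known blocks, so knowledge of one patient's arm carries over to the others in that block.

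Two things would be at stake. If the arm became known while the block was still filling, enrolment could be selective. If it became known later, block-mates still in follow-up could be handled differently in diet counselling, adverse-event recording or judgements of compliance, all of which site staff carry out. Disclosing the length brings the trial no benefit.

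Separately, the description of the list should be reproducible from its own figures, and it is not.

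**Working it through.** **List size (Section 5.2).** Centres x blocks x block length = 9 x 25 x 4 = 900, which is 100 per centre. The stated 999 is 99 higher (99/900 = 11%). It cannot be made from complete blocks of 4: 999/4 = 249.75, and 999/9 = 111 per centre = 27.75 blocks. Ten centres would give 1000, but the text says nine. Three-digit numbers from 100 to 999 number exactly 900, so 999 may be the last number and not the count. The protocol does not say so.

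**What one unmasking gives.** I take each block to hold two A and two B, as 1:1 allocation implies.

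- One patient known: two of the other three are on the opposite arm, so each block-mate is on that arm with probability 2/3 instead of 1/2.
- Two known on the same arm: the other two are certain.
- Two known on different arms: the other two stay at 1/2.
- Three known: the fourth is certain.

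**Ceiling, if every earlier allocation is known.**

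- Certain share: the fourth position always, the third in 1/3 of blocks, so (1 + 1/3)/4 = 33.3%, or about 97 of 290.
- Correct guesses: (1/2 + 2/3 + 2/3 + 1)/4 = 70.8%.

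**The same ceiling with undisclosed mixed block lengths** (illustrative choices, by simulation).

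| Block lengths | Certain | Correct guess |
|---|---|---|
| Fixed 4, known | 33.3% | 70.8% |
| 4 and 6 mixed | 5.6% | 69.1% |
| 4, 6 and 8 mixed | 2.2% | 67.8% |

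Mixing removes most certain allocations but hardly changes average guessing.

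**How much week-8 LDL-C reveals.** Section 6.3 assumes a difference of 7.5 mg/dl and an SD of 20 mg/dl for the change. With normal changes and equal SDs, the best guess of one patient's arm is right with probability Φ(7.5/(2 x 20)) = Φ(0.1875) = 57.4%. Carried to a block-mate, this becomes 0.574 x 2/3 + 0.426 x 1/3 = 52.5%.

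**When the clue arrives.** Taking 6 months as 26 weeks, 25 to 60 patients per centre is 0.96 to 2.3 per week. The fourth patient then enters on average 3/0.96 = 3.1 to 3/2.3 = 1.3 weeks after the first. With steady Poisson entry:

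- The gap exceeds 8 weeks (the S8 result) in under 2% of blocks, even at 25 per centre.
- The gap exceeds 4 weeks (the S4 visit, where adverse events are first collected on schedule) in about 26% of blocks at 25 per centre and 0.5% at 60.

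**The case against.** The strongest reply is that nothing can be deduced while the blind holds. The 33% and 71% figures need every earlier allocation to be known, and nothing in this double-blind trial supplies that. LDL-C at week 8 is a weak clue and almost always comes after the block has filled, so it offers essentially no route to selective enrolment. The primary endpoint is a laboratory value that is also measured centrally. All of this stands, and it keeps the risk modest.

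A reader might also infer from Section 4.1 that bowel symptoms unmask the active arm. The text does not support that. It says such symptoms may occur early and then disappear, and it nowhere says that the cellulose placebo is free of them.

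On the list size, the reply is that 999 is probably the last number on a three-digit list. The food diary in Annex 6 has three boxes for the randomisation number, which fits, although the 24-hour reminder in Annex 7 has two. This is a plausible explanation, but the protocol does not give it.

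The reply does not remove the disclosure itself. Section 9.4 foresees real code breaks with only a conditional safeguard for the investigator, and a printed block length turns one break into information about up to three other patients. Those patients may still be in follow-up after their block has filled.

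**Conclusion.** The point holds as a modest, avoidable weakness together with a correction of record. Section 5.2 gives investigators a single fixed block length and an entry order that locates the blocks. One true unmasking moves each block-mate from 1/2 to 2/3, and two on the same arm settle the block.

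The documents do not support reading this as a third of allocations being predictable in practice, or as evidence that enrolment will be selective: 33% and 71% are theoretical ceilings. The timing figures assume steady recruitment within the Section 6.5 range, and the 57% rests on the planning values in Section 6.3. Uneven recruitment or early spontaneous symptom reports could leave somewhat more exposure.

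Nor does 999 against 900 point to a faulty allocation or a power problem. Either total exceeds the 290 planned, and 100 places per centre exceeds the 25 to 60 expected.

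**What to change.** 1. Delete the block length and the number of blocks from Section 5.2, and hold them in a randomisation document closed to site staff and to anyone else who must stay blind. The cost is one clause in an amendment. Staff who have already read the present text will still know the length of the present list, so this protects less if that list is kept.
2. Vary the block length at random only if the list can still be regenerated before numbered supplies are packed and the first patient is enrolled. The list is said to be programmed already, and Visit S0 issues medication by randomisation number, so later regeneration could disturb the supplies. The gain is mainly fewer certain allocations. The price is a slightly larger possible imbalance at the end of each centre's list.
3. Make the list size agree with its construction (900), or state that 999 is the last number and not the count. If the block details move to the restricted document, make the correction there too. This costs nothing and changes no analysis.
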